### Statistical analyses

#### 
Primary aim.

Descriptive and simple comparative statistics (such as t-tests/ANOVA or χ^2^, as appropriate) will be used to: compare recruitment rates between channels; evaluate retention rates to second appointment and remote session, data and sample completeness, and time taken for each appointment; and assess the distribution of hearing conditions and demographic characteristics recruited through each channel.

The feasibility of recruiting into the Nottingham Hearing BioResource through the tested channels will be assessed based on their relative recruitment rates (mean number of participants per month), the resulting retention rates, and the diversity of the samples recruited. We are aiming for 80% retention to the end of the study; a figure lower than 50% will decrease our ability to maintain a usefully longitudinal BioResource indicating that we may need to put in place extra measures to increase participants’ long-term interest. The distribution of participants in terms of hearing health and other demographic features will give an indication of how broad and balanced a dataset can be achieved with our current recruitment methods and allows us to plan improvements where necessary. The BioResource needs to recruit participants that reflect the wider population they are recruited from in order to benefit everyone in that population. We also need to capture a wide range of people with different hearing disorders to enable stratification of those hearing disorders based on phenotypic descriptors.

We will also look at the success of the testing process; if a section of the protocol has a high rate (>50%) of incomplete data, its future inclusion in the BioResource may be revised or reconsidered. With respect to the time taken to complete the in-person data collection, we are aiming for 1.5 hours (to allow the overall appointment to take no longer than 2 hours); if the distribution of times is skewed towards > 1.5 hours, action may need to be taken to reduce this (taking into account participants’ satisfaction with the process).

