## Materials and methods

### Aim, design and setting

This is a feasibility study recruiting from the general population in the East Midlands region of the United Kingdom. The primary aim of this study is to evaluate; the feasibility of administering a large audiological test battery (deep phenotyping, as detailed in the Processes and measures section below) in adults with and without hearing disorders, how well we can recruit participants to take part, and whether we can retain them for repeated testing.

The primary objectives are to evaluate: the recruitment and retention rates achieved through the tested recruitment channels, the data and sample completeness achieved and the time taken for each appointment, and the distribution of hearing conditions and demographics recruited through each channel. How we will use these metrics to evaluate feasibility is described in the Statistical analyses section below. We hypothesise that the test battery and repeated assessments will be acceptable to the general population.

The secondary aim of this study is to determine the test-retest reliability and co-variability of our test battery of audiological phenotyping tests. The objectives are: to calculate test-retest metrics (as described in the Statistical analyses section below) when audiological tests and questionnaires are carried out 3 months apart, and to investigate any correlations between the results of different audiological tests and other collected measures.

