#### Sample selection.

Participants will be recruited through social media posts, advertising in private sector audiology settings, public engagement at local events, and through the NIHR Nottingham BRC Hearing Theme volunteer database of people who have expressed an interest in taking part in research*.* This will provide evidence of the potential demographic distribution of cohorts recruited in these ways and what the recruitment and retention rate could be for our BioResource.

Participants will receive an inconvenience allowance of £10, and up to £15 travel costs, for each in-person appointment.

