#### Sample size.

We have set a pragmatic target of 84 participants. This is equivalent to approximately 2 months recruitment into the future BioResource based on a projection of recruiting 2500 participants over 5 years. Recruitment will continue for up to 12 months until 84 participants have been recruited. This study does not require any grouping of participants, or any randomisation or blinding.

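### Significance tests between recruitment channels are planned on a sample not sized for them; per-channel estimates with 95% intervals would serve the primary aim better

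*Protocol article*

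**What the plan says.** The Aim, design and setting section lists among the primary objectives "the recruitment and retention rates achieved through the tested recruitment channels" and "the distribution of hearing conditions and demographics recruited through each channel". Sample selection names four routes: "through social media posts, advertising in private sector audiology settings, public engagement at local events, and through the NIHR Nottingham BRC" Hearing Theme volunteer database.

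For analysis, the Primary aim part of Statistical analyses states: "Descriptive and simple comparative statistics (such as t-tests/ANOVA or χ^2^, as appropriate) will be used to: compare recruitment rates between channels". The sentence goes on to retention at two points, completeness and appointment time, and then to hearing conditions and demographics by channel. The next paragraph says that the feasibility of recruiting through the tested channels will be judged on monthly recruitment rate, retention and diversity together.

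On numbers, the Sample size section says "We have set a pragmatic target of 84 participants" and explains: "This is equivalent to approximately 2 months recruitment into the future BioResource based on a projection of recruiting 2500 participants over 5 years". It gives no expected number per channel.

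**The concern.** The Abstract says the findings will show which channels work well and will feed the recruitment strategy of the BioResource. Hypothesis tests are a weak tool for that question when the sample was set by throughput and is then divided among four channels. A non-significant result may be read as meaning that the channels perform alike, although the test had little chance of separating them. Conversely, with several metrics tested, one chance difference may be read as showing that a particular channel is better. The protocol already uses intervals elsewhere: the Secondary aim section asks for 95% confidence intervals on the intraclass correlations. The channel comparisons, which belong to the primary aim, have no such requirement.

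**Working it through.** **The plan's own figure.** 2500 participants / 60 months × 2 months = 83.3, rounded up to 84. The figure reproduces. It is a throughput projection and contains no effect size, alpha or power.

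**Inputs.**
- From the protocol: 84 participants, four channels, a retention aim of 80% and a concern level of 50%. Both retention levels are worded for the whole study and are borrowed here only as an effect size.
- Assumed: two-sided alpha of 0.05 without adjustment, and either an even split of 84/4 = 21 per channel or an uneven split of 50/20/9/5.

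**Power of the four-channel chi-square (3 df, critical value 7.81).** The statistic is Σ nᵢ(p̂ᵢ − p̄)² / [p̄(1 − p̄)]. Power was simulated, because the large-sample approximation is poor in a channel of 5. In the uneven split, the last-listed proportion belongs to the channel of 5.

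| True proportions by channel | 21/21/21/21 | 50/20/9/5 |
|---|---|---|
| 30/30/30/50% | 25% | 12% |
| 5/5/5/20% | 34% | 26% |
| 20/30/40/50% | 41% | 36% |
| 80/80/80/60% (retention) | 31% | 16% |
| 80/80/80/50% (retention) | 59% | 27% |

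Check on the bottom row, even split: p̄ = 0.725, and the noncentrality is 21 × (3 × 0.075² + 0.225²) / (0.725 × 0.275) = 7.11, which gives 60%. For the uneven split the same approximation gives 23%, against 27% simulated.

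**Recruitment counts.** Here the information lies in all 84 recruits, not in 21 per channel. If all channels run for the same period, equal rates mean equal shares, and the noncentrality is 84 × Σ(qᵢ − 0.25)² / 0.25.
- Shares 40/20/20/20%: 84 × 0.03 / 0.25 = 10.08, power about 76%.
- Shares 50/25/15/10%: power above 99%.
- Shares 30/30/20/20%: power about 31%.

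**Chance differences.** With m independent tests, the probability of at least one false positive is 1 − 0.95^m.
- m = 5 (recruitment, two retention points, two case-mix variables): 23%.
- m = 7 (four case-mix variables): 30%.
- The figure passes 50% only at m = 14 (51%).
- Correlation lowers it. For 8 tests, simulation gave 34%, 25% and 16% at correlations of 0, 0.5 and 0.8.

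**What an interval would show.** The Wilson 95% limits are [p̂ + z²/2n ± z√(p̂(1 − p̂)/n + z²/4n²)] / (1 + z²/n), with z = 1.96.
- 17 of 21 retained (81%): 60% to 92%.
- 4 of 5 retained (80%): 38% to 96%, which covers both the 80% aim and the 50% concern level.

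**The case against.** The strongest reply is that nothing in the protocol turns on a p-value. Channels are to be weighed on yield, retention and diversity together. The retention, completeness and time benchmarks are descriptive and are not set by channel. Descriptive statistics are already promised in the same sentence as the tests. The article is also a condensed account, so alpha, a hierarchy or an exploratory label may sit in a fuller plan. All of this stands, and it limits the point to a change of method.

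Several stronger readings are tempting, and the documents do not support them:
- A reader might infer that a false difference is likely. At 5-7 tests it is well below even odds, and the protocol does not fix the number of tests.
- A reader might infer that real differences are mostly missed. That fits small and moderate differences in retention or case mix. It does not fit clearly unequal recruitment counts, or an ANOVA with a large effect (f = 0.40 has about 87% power with 21 per channel).
- A reader might take 21 per channel as the plan's figure. It is only 84/4.
- A reader might count completeness and appointment time as channel comparisons. The sentence evaluates them without mentioning channel.
- A reader might see a contradiction with the Sample size statement that "This study does not require any grouping of participants, or any randomisation or blinding". Placed beside randomisation and blinding, grouping can be read as allocation to study groups, which does not rule out analysis by channel.

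The reply does not change the arithmetic. A later analysis plan could add an alpha or a ranking of metrics, but it could not make 84 people split four ways informative enough for a test of moderate differences.

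**Conclusion.** The point holds as a cheap improvement. The protocol names between-channel significance tests for a primary objective on a sample that was not derived from any comparison. For moderate differences in retention or case mix those tests would usually be non-significant even with even channels. With one channel at the protocol's concern level and three at its target, they would miss the difference about 4 times in 10 (59% power), and about 7 in 10 (27% power) under the uneven split. These figures depend on the assumed split and alpha. The risk is one of interpretation, since no rule requires a channel to be chosen or abandoned on a test.

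**What to change.** In the Primary aim part of Statistical analyses, make estimation the basis for comparing channels:

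- For each channel, report the monthly recruitment rate, retention to the second appointment and to the remote session, and the hearing-condition and demographic proportions, each with a 95% confidence interval.
- Report between-channel differences in these quantities with 95% confidence intervals.
- Label all between-channel comparisons exploratory.
- State that no channel will be preferred, dropped or treated as equivalent on a significance test.

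This needs no extra participants or data and about the same analysis effort, and it affects only analysis and reporting. The cost is that the study could no longer claim significant differences between channels and would have to show wide intervals, such as 60-92% for 17 of 21.

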Participants in the Nottingham Hearing BioResource, with and without hearing or ear problems, will undergo a series of in-depth tests to measure different aspects of hearing and ear health. Participants will also complete questionnaires to provide information about their hearing and general health, and provide samples such as hair and blood for biomarker and genetic analyses. The aim of the BioResource is to follow participants as they age, by periodically repeating tests and questionnaires, and adding new tests as necessary, to allow researchers to link together different aspects of data, identify long-term patterns (e.g., whether lifestyle changes can reduce a person’s susceptibility to experiencing tinnitus), and identify distinct groups of patients with similar phenotypes. Our aim is to leverage the power of large, accessible datasets in a way that can transform how we treat and manage hearing loss and hearing-related conditions in the future; a future where the population is ageing and the need for effective treatments is set to increase [22].

The protocol described here is for a feasibility study; a sample of participants will be recruited and tested to ensure that the core processes put in place, including recruitment channels, audiological test pipelines, and follow-up scheduling, are all working effectively. The population intended to participate in this research will be adults with or without hearing loss, tinnitus or any other hearing condition. We are not targeting any particular hearing conditions in our recruitment for the feasibility study. Efforts will be made to ensure that recruitment occurs across a broad spectrum of the population and results will be analysed with respect to this.

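### Diversity is assessed on the people recruited and the retention targets name no demographic or hearing group, so the study could meet its 80% aim and look diverse while one group is selectively lost

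*Protocol article*

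**What the plan says.** The Protocol article is the only document shown.

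- **Objective.** Aim, design and setting ties recruitment and retention rates to the tested channels. It lists separately "the distribution of hearing conditions and demographics recruited through each channel".
- **Criteria.** In Statistical analyses (Primary aim), retention to the second appointment and to the remote session is to be evaluated, with no demographic or hearing breakdown named. Feasibility of recruiting through the channels rests on recruitment rates and on "the resulting retention rates, and the diversity of the samples recruited".
- **Targets.** "We are aiming for 80% retention to the end of the study", and "a figure lower than 50% will decrease our ability to maintain a usefully longitudinal BioResource". Neither figure refers to a group.
- **Purpose.** The same section says "The BioResource needs to recruit participants that reflect the wider population they are recruited from in order to benefit everyone in that population", and uses the participant distribution to indicate how broad and balanced the eventual dataset could be. The Introduction states: "The aim of the BioResource is to follow participants as they age, by periodically repeating tests and questionnaires".
- **Size.** "We have set a pragmatic target of 84 participants", described as "equivalent to approximately 2 months recruitment into the future BioResource based on a projection of recruiting 2500 participants over 5 years".

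**The concern.** The criteria look at diversity when people enter and at retention as a rate without groups. Neither shows who remains. For a resource built on repeated measurement, the breadth that matters includes breadth among people with repeat data. If loss falls mainly on one age band, ethnic group or hearing group, both criteria can be satisfied while the longitudinal part of the dataset is much narrower than the recruited sample.

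What is at stake is the conclusion on breadth and balance, which is meant to guide recruitment to the future resource. A favourable reading could leave a group under-served for years, because nothing in the stated criteria would prompt measures to keep that group. The Participants section says that people without known hearing problems will be needed as a future control group, so their return matters as well as their enrolment.

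**Working it through.** **Inputs.** Recruitment target 84, and the projection of 2500 over 5 years (Sample size). Retention aim 80% and concern mark 50% (Statistical analyses, Primary aim). The article gives no group shares and no retention by group, so the shares below are assumptions.

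**The plan's own figure.** 2500 / 60 months × 2 months = 83.3, which agrees with 84. It is a pragmatic target, and there is no power calculation to reproduce.

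**What the 80% aim permits.** 0.80 × 84 = 67.2, so at least 68 must be retained: 68/84 = 81% (exact 95% CI 71% to 89%). Up to 84 − 68 = 16 people may be lost.

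**Worst case: all 16 losses fall on one group first.**

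| Assumed share of recruits | Group size | Retained in group | Retained in the rest |
|---|---|---|---|
| 10% | 8 | 0/8 = 0% | 68/76 = 89% |
| 15% | 13 | 0/13 = 0% | 68/71 = 96% |
| 20% | 17 | 1/17 = 6% | 67/67 = 100% |
| 25% | 21 | 5/21 = 24% | 63/63 = 100% |
| 30% | 25 | 9/25 = 36% | 59/59 = 100% |

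Overall retention is 81% in every row.

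**Less extreme: about 90% retained in the rest, 68 retained overall.**

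| Assumed share | Retained in the rest | Retained in group | Group's share of the 68 retained |
|---|---|---|---|
| 15% | 64/71 = 90% | 4/13 = 31% | 4/68 = 6% |
| 20% | 60/67 = 90% | 8/17 = 47% | 8/68 = 12% |
| 25% | 57/63 = 90% | 11/21 = 52% | 11/68 = 16% |
| 30% | 53/59 = 90% | 15/25 = 60% | 15/68 = 22% |

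**Would a table by group show it at this sample size?** In the 20% case, 8/17 has an exact 95% CI of 23% to 72%, and Fisher's exact test against 60/67 gives p = 0.0004. By the normal approximation (two-sided 5%), power to detect 50% against 87% retention is about 83% to 94% for groups of 13 to 25. For 60% against 87% it is about 63% to 77%. Exact tests would have somewhat less. The table would show gross differential loss. Smaller differences can only be estimated, with wide intervals.

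**The case against.** The strongest reply is that this is table layout, which a condensed article may leave to an analysis plan. The article promises descriptive and simple comparative statistics for retention and excludes no breakdown. That answers any charge of incompleteness. It does not answer the point here, because the article itself sets the feasibility criteria, attaches diversity to the recruited sample, and then draws a conclusion about the dataset of a longitudinal resource.

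The criterion sentence concerns the feasibility of recruiting, and for that question recruited diversity is the right measure. This stands, and it is why the recruited distribution must be kept.

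Other text touches the issue without settling it. The Introduction says results will be analysed with respect to breadth, but the breadth it describes is that of recruitment. Reasons for non-attendance are invited (Participant viewpoint), but they are voluntary and not tied to groups. Telephone and postal options (Remote follow-up) reduce one likely cause of selective loss at the last stage. The bar on comparing participants by hearing status (Secondary aim) concerns test measures, so it does not prevent a retention table.

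A reader might go further in three ways that the text does not support:

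- That retention will be broken down only by channel. The objective names channels, but nothing says that no other breakdown will be made.
- That representativeness will be judged only by comparing channels with one another. The article names the wider population as its yardstick and does not say this.
- That diversity should be judged on remote-session completers instead of recruits. This would discard the stated recruitment objective. It would also leave out people who attended both in-person appointments and so already have repeated deep phenotyping. The remote session covers only the five questionnaires and the online listening test.

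**Conclusion.** The point holds as a gap between the stated criteria and the conclusion they are meant to support. Under an assumed 20% share, the study can report 81% retention and a diverse recruited sample while a group is retained at 47% against 90% elsewhere and its share drops from 20% to 12%. Under an assumed 15% share, the whole group could be lost with the aim still met.

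The size depends on assumed shares and assumed differential loss. The article gives neither, and selective loss is a possibility, not a finding. The 80% and 50% figures are prompts for action rather than stop rules, so the consequence is a misleading conclusion on breadth and not a wrong go/no-go decision. A reader might infer that very uneven loss would always pass unnoticed, but the aim does limit it. For example, an equal 42:42 split retained at 90% and 50% gives (37.8 + 21)/84 = 70% overall, which already misses the 80% aim.

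**What to change.** In the primary analysis:

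1. Keep the distribution of the recruited sample by channel.
2. Beside it, report the make-up of those attending the second appointment and of those completing the remote session, by age, sex, ethnicity and self-reported hearing-condition status, using the demographics that are collected.
3. Give retention to each of the two stages by these groups, with 95% confidence intervals.
4. Base the conclusion on breadth and balance on both the recruited and the retained samples, and treat second-appointment attenders as the sample with repeated deep phenotyping.

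The cost is a change of wording and some extra table columns. Participant characteristics, self-reported hearing status and attendance are already part of the study, so no participant procedure changes. The drawback is imprecision: at 84 participants the group estimates should be presented descriptively, not as tests of equal retention.

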Bone conduction audiometry	Standard procedure used in audiometry clinics to assess hearing thresholds at varying frequencies using bone conduction to bypass the outer/middle ear.	Test-retest threshold difference of 5.1 dB (5.3 SD) [46]. Good test-retest reliability; mean dB HL difference under 5 dB at all frequencies [43].
Extended high-frequency audiometry	Pure tone audiometry at frequencies higher than 8 kHz.	Good test-retest reproducibility. E.g., within 2 dB at all frequencies [47], and test-retest repeatability within 10 dB for 94% of measurements at 8 to 16 kHz [45].
Quick Speech In Noise test (QuickSIN)	Measures the SNR (signal-to-noise ratio) a listener requires to understand 50% of key words in sentences in a background of babble.	Estimated accurate to +/-2.7 dB at the 95% confidence level. Test-retest standard deviation of 1.4 dB SNR for hearing-impaired [34]. Correlation between scores not significant (r = 0.34 [95% CI, − 0.08 to 0.68]) [43].
Wideband Tympanometry (WBT)	Measures middle ear function using wideband acoustic immittance under varying ear-canal pressures.	Test-retest reliability excellent (immediate test–retest without reinsertion of the probe), for comparison statistics see papers [48, 49].
Wideband Middle Ear Muscle Reflex (MEMR) test	Changes in MEMR amplitude (bilateral contraction of the middle ear stapedial muscle in response to moderate-to-high intensity acoustic stimuli) have been proposed as an assessment for noise-induced synaptopathy.	High test-retest reliability when elicitor stimuli presentation levels are between 70 and 90 dB SPL (moderate reliability at 60–65 dB SPL, low at 45–50 dB SPL). For details, see [50].
Otoacoustic Emissions (OAE); Transient Evoked (TE) and Distortion Product (DP)	OAEs are sounds of cochlear origin produced by sensory outer hair cells in response to auditory stimulation, and are used to test the function of the middle and inner ear. TEOAEs are evoked by a broadband click. DPOAEs are evoked by two simultaneously presented pure-tones.	Overall, test-retest reliability of TEOAEs and DPOAEs is high, but reliability decreases after probe-refitting and with longer time intervals (figures in [51]). Test–retest reliability of DPOAE is good at 1.5 kHz (ICC = 0.78, 95% CI 0.48 to 0.91) and excellent at 4 kHz (ICC = 0.91, 95% CI 0.76 to 0.97) [50]. DPOAE: percentage agreement high, ranging from 78% to 100% [43].

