#### Participant viewpoint.

At the in-person appointments, participants will additionally be asked hypothetical questions as to whether they would be willing to join the Nottingham Hearing BioResource, whether they would be willing to give a blood sample to take part in that BioResource, and whether they would be happy for that blood sample to also contribute to the national NIHR BioResource [10].

After each stage of the study, participants will be asked about their satisfaction with the process, whether they have any suggestions for improving the participant experience, and whether they have any reservations about continuing in the study. Participants that fail to attend their second appointment or to complete the remote online session will be given the opportunity to provide their reasons why and these will be documented.

### 
Data management

Data collection throughout the study will be continually monitored and analysed to ensure quality and to monitor the efficiency of different recruitment approaches. Reasons for missing data will be logged (e.g., a test may be abandoned because the participant is uncomfortable) and the reasons will be analysed to determine improvements to the data collection process for the BioResource.

A data management plan is in place. Data will be securely collected and managed using the REDCap [53] electronic data capture tool hosted at the University of Nottingham, and stored in a MySQL database [54]. Personal information will only be accessible to researchers administering the study. Data exported for analysis by the research team will be de-identified.

Data from the feasibility study will be made available to external researchers on request. The data will be findable through a Digital Object Identifier (DOI) in the Nottingham Research Data Management Repository [55], providing metadata and instructions on how to request a dataset. Data shared with external researchers will be pseudonymised (with keys unique to each extraction) and de-identified before sharing.

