### Safety considerations

There are minimal risks to the participants taking part in this study; all tests are minimally invasive and have no known side effects. There is a chance of incidental findings, such as undiagnosed hearing loss, and affected participants will be advised to contact their General Practitioner.

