#### Secondary aim.

Intraclass correlation coefficients with 95% confidence intervals and Bland–Altman plots will be used to assess the test-retest reliability of the audiological phenotyping tests and PROMs performed 3 months apart. These test-retest metrics will be compared to previously published information about the reliability of these tests (see Table 1) to assess the accuracy and reliability of these tests in our hands. Where no test-retest results have been previously published, for example, for SSQ12, our results will add to the field. Establishing the possible magnitude of the difference in results when tests are repeated soon after each other allows meaningful changes in results, when tests are repeated over longer time periods, to be identified.

Spearman’s rank or Pearson’s correlation coefficients and regression analysis, as appropriate, will be used to investigate relationships between different audiological tests, between audiological tests and PROMs, and between tests/PROMs and hair cortisol levels. To perform these analyses, audiological tests and PROM questionnaires will be converted into final scores as appropriate, for example, pure tone audiometry results will be converted into better/worse-ear across-frequency averages, and the SSQ12 produces an overall score out of 10. Consistent correlations between measures may inform the inclusion/exclusion of redundant measures in the deep phenotyping protocol used in the Nottingham Hearing BioResource. No analyses will be performed for the feasibility study to explicitly compare measures between participants grouped by hearing loss/hearing condition status, but this will be considered as a potentially confounding factor when looking at correlations between measures.

### 
Status and timeline

Recruitment and enrolment began on 7^th^ October 2024 and will cease after 12 months (6^th^ October 2025) or when 84 participants have been recruited. Participants will be involved in the study for approximately 5 hours over a maximum of 7 months (the second appointment is within 3 months of the start and the remote follow-up is within 3 months of the second appointment, both within a 2-week window).

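### The only numeric completeness criterion is pooled over all participants, so it would not flag selective loss of the MEMR test in a sound-intolerant minority

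*Protocol article*

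**What the plan says.** The Aim, design and setting section puts the feasibility question for a mixed population: whether the battery can be administered "in adults with and without hearing disorders". The Introduction adds that the study's data will support or refute future inclusion of MEMR.

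The Primary aim part of the Statistical analyses section gives one numeric criterion for completeness: "if a section of the protocol has a high rate (>50%) of incomplete data", then "its future inclusion in the BioResource may be revised or reconsidered". It names no subgroup. In the same section, the distribution of hearing conditions is to be assessed by recruitment channel; completeness is not tied to hearing condition.

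Four other places bear on the point:
- The Introduction describes hyperacusis as reduced sound tolerance and calls it common. It is not among the exclusion criteria.
- Table 1 describes MEMR as a reflex elicited "in response to moderate-to-high intensity acoustic stimuli".
- The Data management section says reasons for missing data are logged, with the example that "a test may be abandoned because the participant is uncomfortable", and that these reasons will be analysed to improve data collection.
- The In-person appointments section puts the self-report of hearing problems and the Hyperacusis Questionnaire (HQ) before the audiological tests.

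**The concern.** The aim concerns people with and without hearing disorders, but the criterion is one majority threshold over everyone. If a component fails only in a minority, the pooled rate stays low and the criterion says nothing.

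MEMR is the clearest case, because the protocol itself supplies the elements: a stimulus of moderate to high intensity, eligible participants with reduced sound tolerance, and stopping for discomfort as a foreseen reason for missing data. If those participants stopped MEMR selectively, the criterion would not prompt anyone to reconsider it. The full BioResource would then lack MEMR data systematically in one of the conditions it wants to characterise. The Primary aim section itself says a wide range of hearing disorders must be captured.

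**Working it through.** **Inputs from the protocol.** Target sample of 84 (Sample size section: "We have set a pragmatic target of 84 participants"); threshold above 50% incomplete (Statistical analyses, Primary aim).

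**Inputs assumed.** The sound-intolerant share *p* (the protocol says only that hyperacusis is common), complete abandonment of MEMR in that group, and the incomplete rate *b* among everyone else. The main case uses *p* = 10–20% and *b* = 5%.

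**The plan's own figure.** 2500 participants over 60 months, for 2 months: 2500/60 × 2 = 83.3, rounded up to 84. It reproduces.

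**Count needed.** More than half of 84 is at least 43 participants with incomplete data.

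**Pooled incompleteness** = *p* + (1 − *p*) × *b*.
- *p* = 0.10: 0.10 + 0.90 × 0.05 = 0.145, or 84 × 0.145 ≈ 12 participants.
- *p* = 0.20: 0.20 + 0.80 × 0.05 = 0.24, or 84 × 0.24 ≈ 20 participants.

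Both are far below 43. If each of 84 participants is independently incomplete at these rates, the binomial probability of 43 or more is about 3 × 10⁻¹⁵ and 7 × 10⁻⁸.

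**Share needed to reach the threshold** with *b* = 0.05: (0.50 − 0.05)/0.95 = 0.474, or 84 × 0.474 ≈ 40 people, all of them abandoning the test.

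**Sensitivity to the assumptions (N = 84, whole subgroup abandons MEMR).**

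| Share *p* | Others' incomplete rate *b* | Pooled rate | Probability of 43 or more |
|---|---|---|---|
| 10% | 0% | 10% | 2 × 10⁻²¹ |
| 20% | 0% | 20% | 2 × 10⁻¹⁰ |
| 20% | 10% | 28% | 6 × 10⁻⁶ |
| 20% | 20% | 36% | 0.003 |
| 30% | 0% | 30% | 4 × 10⁻⁵ |
| 30% | 10% | 37% | 0.006 |
| 40% | 0% | 40% | 0.025 |
| 40% | 10% | 46% | 0.20 |

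For the pooled rate to reach 50%, the others would need an incomplete rate of (0.50 − *p*)/(1 − *p*): 44% at *p* = 10%, 37.5% at 20% and 29% at 30%. A loss of that size in everyone else would be a problem in itself.

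**Looking within the group.** With 8 or 17 people in the group (10% or 20% of 84), the same rule of more than half incomplete is met as follows:
- true abandonment 80%: probability 0.94 (n = 8) and 0.997 (n = 17);
- true abandonment 20%: probability 0.010 and 0.003;
- true abandonment 50%: probability 0.36 and 0.50.

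A within-group look therefore separates gross failure from good tolerance, but not cases in between. The precision is limited: if 8 of 8 stop, the exact two-sided 95% interval has a lower limit of 0.025^(1/8) = 0.63; for 17 of 17 it is 0.025^(1/17) = 0.80.

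**The case against.** The strongest reply is that the threshold carries less weight than the calculation suggests. Several stronger readings are tempting, and the document does not support them.

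- **That the pooled rule is the only information on tolerability.** It is not. Reasons for missing data are logged and analysed, with discomfort as the named example. Participants are asked about satisfaction and reservations after each stage. A run of stops on MEMR would be visible there.
- **That 50% or less counts as a pass.** The protocol does not say so. Crossing the threshold is an advisory prompt, and nothing is declared feasible below it. Reliability and redundancy with other measures also inform what is kept.
- **That the Secondary aim section forbids the split.** It says "No analyses will be performed for the feasibility study to explicitly compare measures between participants grouped by hearing loss/hearing condition status". That sentence concerns measures, in a paragraph on scores and correlations. Completeness belongs to the primary aim, where simple comparative statistics are planned.
- **That the Safety considerations section contradicts the Data management section.** The statement that "all tests are minimally invasive and have no known side effects" is compatible with a participant finding a test uncomfortable and stopping.

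It is also fair to say that the scenario is assumed. The protocol gives neither the share with hyperacusis nor an abandonment rate, and the article does not give the study's own MEMR presentation levels. Whether each test is its own section is not stated either. Detailed table layouts can be left to an analysis plan.

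All of this stands, and it limits the point. It does not remove it: the article does fix a criterion, that criterion does not match the population named in the aim, and the logged reasons carry no stated split by condition and no criterion.

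**Conclusion.** The point holds as a mismatch between the aim and its one numeric completeness criterion. Under total abandonment of MEMR by a sound-intolerant group of 10–20%, with 5% loss in the others, pooled incompleteness is 14.5–24% against a threshold of 50%. The group would have to exceed about 47% of the sample before reconsideration was prompted. The result is insensitive to the assumed share as long as that share is well below half and loss in the others is modest.

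The consequence is a missed prompt, not a false declaration of feasibility. The free-text and logged information could still bring the problem to light, but nothing in the protocol ensures that it is read by condition. The change is worth making because it is nearly free and lets the criterion answer the question the study asks.

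**What to change.** Keep the pooled figure and add to it:

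1. For each section, report completeness and the number stopped for discomfort as n/N with an interval, in participants with and without a self-reported hearing condition.
2. For MEMR, report the same by HQ score, with any grouping of the score fixed before the completeness data are examined.
3. State that high incompleteness within a group prompts the same reconsideration as high pooled incompleteness.
4. State whether each test counts as a section.

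The HQ and the self-report come before the sound tests at the same visit, so they should be available even when MEMR is stopped. The reasons are already logged. Only the analysis and a few table rows change, which is possible although recruitment has begun. The downside is small and imprecise subgroup counts, so the group figures should inform judgement and not act as automatic decisions.
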